### Data collection and monitoring

All postoperative complications will be monitored during hospital stay and follow-up of 2, 6, 12 weeks after discharge. The questionnaires (QLQ-C30/PAN-26) are filled in by the patient on the day of randomization, after two weeks of drainage when randomized for PBD, and three and six weeks after discharge from admission for surgery. There will be regular contact between the trial coordinator and the participating centres. The trial coordinator will monitor the data of every included patient.

### Data analysis

The study is designed as an equivalence trial with respect to the primary outcome measure and superiority with respect to the secondary outcome measures. The principal analysis consists of an intention-to-treat comparison of the severe complication rate in both treatment strategies. The comparison will be expressed in terms of a relative risk and 95% confidence intervals. The research hypothesis will be evaluated using a two-group large-sample normal approximation test of proportions, with a one-sided 0.05 significance level. In addition, a comparison of the incidence of complications over time will be made using Kaplan-Meier estimates.

Subsequent analyses are directed at the secondary endpoints. The total number of additional procedures, the length of hospital stay, hospital-free survival and total costs will be compared using t-test statistics. Preplanned subgroup analyses include type of surgery (resection versus bypass), severity of jaundice and other risk factors for complications such as age > 70 years, weight loss > 10%, low albumin levels, renal function, low Hb (< 7 mmol/l), tumor pathology (papilla neoplasms, pancreatic head neoplasms and distal bile duct neoplasms).

An independent safety committee, consisting of three specialists (dept of internal medicine, dept of surgery, dept of clinical statistics), will guarantee the safety of the patients. After 105 included patients (50%), a blinded interim-analysis will be performed of all endpoints. Because of the delayed response for determination of the primary endpoint (severe complications), this analysis will be performed 120 days after randomization of the last patient to reach n: 105. The nominal significance (sequential two-sided testing) for the stopping rule is p < 0.01 (α = 0.01) for adverse effects (severe complications principal endpoint of safety analysis). Analysis will be performed for the individual groups and for the principal adverse effects.

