**Methods/design:**

Patients with obstructive jaundice due to a periampullary tumor, eligible for exploration after staging with CT scan, and scheduled to undergo a "curative" resection, will be randomized to either "early surgical treatment" (within one week) or "preoperative biliary drainage" (for 4 weeks) and subsequent surgical treatment (standard treatment). Primary outcome measure is the percentage of severe complications up to 90 days after surgery. The sample size calculation is based on the equivalence design for the primary outcome measure. If equivalence is found, the comparison of the secondary outcomes will be essential in selecting the preferred strategy. Based on a 40% complication rate for early surgical treatment and 48% for preoperative drainage, equivalence is taken to be demonstrated if the percentage of severe complications with early surgical treatment is not more than 10% higher compared to standard treatment: preoperative biliary drainage. Accounting for a 10% dropout, 105 patients are needed in each arm resulting in a study population of 210 (alpha = 0.95, beta = 0.8).

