#### Sample size calculation

The recently performed meta-analysis of randomized clinical trials and comparative studies, addressing the effectiveness of a PBD strategy in jaundiced patients versus a direct surgical treatment, did not show a difference in mortality between the two strategies [37]. The overall complication rates were, summarizing level I and II studies, 42% for the 'early surgery' strategy and 58.1% for strategy with preceding PBD.

The sample size calculation is based on the equivalence design for the primary endpoint, severe complications of treatment. Based on an expected 38% complication rate for early surgical treatment and 48% for preoperative drainage, equivalence is taken to be demonstrated if the percentage of severe complications with early surgical treatment is not more than 10% higher compared to standard treatment with PBD. Accounting for a 10% dropout, 105 patients are needed in each arm resulting in a study population of 210 (alpha = 0.95, beta = 0.8). If equivalence is found, the comparison of the secondary outcomes will be essential in selecting the preferred strategy.

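### The primary test leaves out the stratification factor and the baseline risk factors the plan names; it is valid and matches the sample size, but gives up a modest amount of precision

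*Protocol article*

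**What the plan says.** The Data analysis section of the protocol article fixes the primary comparison: "The principal analysis consists of an intention-to-treat comparison of the severe complication rate in both treatment strategies". The hypothesis is to be evaluated by a "two-group large-sample normal approximation test of proportions, with a one-sided 0.05 significance level". On reporting it says: "The comparison will be expressed in terms of a relative risk and 95% confidence intervals". No covariate is named for this analysis.

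The same section lists subgroup factors, among them "severity of jaundice and other risk factors for complications such as age" over 70, weight loss, albumin, renal function and haemoglobin. They are thus named as prognostic but are used only for subgroups.

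Study design says that randomization is stratified for centre, and Participating centres counts fourteen hospitals. Sample size calculation sets the margin: equivalence is shown if "the percentage of severe complications with early surgical treatment is not more than 10% higher compared to standard treatment with PBD".

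**The concern.** Randomization stratified by centre balances the arms on centre. If centres differ in complication rate, a standard error that ignores centre does not reflect that balance, and the interval is somewhat wider than it need be. The same holds for baseline variables that predict complications.

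An absolute margin does not rule out adjustment. A logistic model standardised over the trial population (g-computation) returns a marginal risk difference on the scale of the margin. It also returns the relative risk that the plan wants to report.

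At stake is some power for the primary conclusion. A prespecified adjustment would also forestall a post hoc argument if a named risk factor turned out unbalanced by chance.

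**Working it through.** **Inputs.** The margin is 10 points and the test is one-sided at 0.05. Power is 80% (printed as beta = 0.8), dropout is 10%, and there are 105 patients per arm. Two pairs of expected rates are printed. The Abstract has "Based on a 40% complication rate for early surgical treatment and 48% for preoperative drainage". Sample size calculation has "Based on an expected 38% complication rate for early surgical treatment and 48% for preoperative drainage". R2 is not in the documents, so a range starting at zero is assumed.

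**Reproducing the plan's figure.** With early-surgery rate pE, drainage rate pD and unpooled variance,

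n = (1.645 + 0.842)² × [pE(1 - pE) + pD(1 - pD)] / (pD - pE + 0.10)².

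- 40% and 48%: 6.18 × (0.2400 + 0.2496) / 0.18² = 93.4, so 94 per arm; 94 / 0.9 = 104.4, so 105. This matches exactly.
- 38% and 48%: 6.18 × (0.2356 + 0.2496) / 0.20² = 75 per arm; 75 / 0.9 = 83.3, so 84. This does not match. At one-sided 0.025 the same rates give 96, or 107 with dropout, which is close.

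The crude calculation at 40% and 48% is therefore the one that yields 105, and the crude test delivers the planned power under those rates.

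**Effect of adjustment by formula.** Adjustment multiplies the variance by (1 - R2). At 94 per arm and 40% versus 48%, the crude SE is sqrt(0.4896 / 94) = 0.0722, and

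power = Φ(0.18 / (0.0722 × sqrt(1 - R2)) - 1.645).

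The one-sided half-width is 1.645 × 0.0722 × sqrt(1 - R2). The equivalent n is 94 / (1 - R2).

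| Assumed R2 | Power, 40% vs 48% | One-sided 95% half-width (points) | Equivalent extra patients per arm | Power, 38% vs 48% |
|---|---|---|---|---|
| 0 | 80.2% | 11.9 | 0 | 87.3% |
| 0.05 | 82.0% | 11.6 | about 5 | 88.7% |
| 0.10 | 83.7% | 11.3 | about 10 | 90.1% |
| 0.15 | 85.6% | 10.9 | about 17 | 91.5% |

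The last column uses a distance of 0.20 and SE = sqrt(0.4852 / 94) = 0.0718. There, R2 of 0.05 to 0.10 adds about 1 to 3 points.

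**Equal true rates of 48%.** Crude power is 39%. It becomes 42% at R2 = 0.10 and 46% at R2 = 0.20.

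**Simulation.** Two sets of assumptions were run at 94 per arm, each comparing a standardised logistic risk difference with the crude test.

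- Five binary risk factors, no centre terms, 3,000 runs per scenario. The change in power was -0.9 points with non-prognostic factors, -0.2 at R2 about 0.04, +1.0 at about 0.10 and +2.9 at about 0.15. Type I error at the margin was 5.6% to 6.3% crude and 5.3% to 6.1% adjusted.
- Three continuous covariates and fourteen centres of assumed size, 2,500 runs per scenario. The gain was about 0.5 to 1 point at R2 about 0.04, 2 to 3 at 0.10 and 5 to 6 at 0.16. Type I error was similar to crude.

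The Monte Carlo standard error of one power near 82% with 3,000 runs is sqrt(0.82 × 0.18 / 3000) = 0.7 points. The smallest differences should therefore not be over-read.

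**Size of the model.** Expected events are 94 × 0.40 + 94 × 0.48 = 82.7, about 83. Fourteen centres would need 13 terms. Under the assumed centre sizes, about 40% of simulated trials had a centre with all or no events. This did not harm the risk difference in those runs, but it calls for a pooling rule.

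**The case against.** The strongest objection is that nothing here is wrong. An unadjusted intention-to-treat comparison is valid under randomization, it is simple, and it is the analysis the trial was sized for. A reader might infer from this point that the primary analysis is invalid or leaves the trial underpowered. The documents do not support that: 105 per arm reproduces exactly under the crude test. That part of the objection stands.

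A reader might also infer that the 10-point margin is tight and that adjustment would relieve it. Under the plan's own rates the expected distance to the margin is 18 to 20 points. The margin is demanding only if the true rates are about equal, and there adjustment moves power only from 39% to between 42% and 46%. The half-width stays above 10 points across the table, so an observed tie would fail with or without adjustment.

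Nor is the precision simply free. R2 is unknown, and weak covariates give no gain or a slight loss. Nothing in the documents shows how prognostic bilirubin, age and albumin are. Collection of all the named factors is implied by the subgroup list, not stated. Bilirubin and age must be known for every patient because they are eligibility criteria (Study population). Albumin is not one. Chance imbalance adds little to the argument, since the crude interval already allows for it.

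Finally, an analysis plan that is not shown may deal with covariates. It could add a supportive adjusted analysis, but to make one primary it would have to override the test that the article names. That is why the point survives.

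**Conclusion.** The point holds as a modest improvement in efficiency. The plan fixes a primary test that omits its own stratification factor and the baseline risk factors it names, although at least centre, bilirubin and age must be available for every patient.

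By formula the gain is about 2 to 5 points of power for R2 of 0.05 to 0.15 at 40% versus 48%. It is about 1 to 3 points for R2 of 0.05 to 0.10 at 38% versus 48%. Simulation puts it between about -1 point with non-prognostic factors and +3 to +6 points at R2 about 0.15. All of this rests on an assumed R2, on 94 evaluable patients per arm and on the one-sided 0.05 level.

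**What to change.** In the Data analysis section, or in the analysis plan before unblinding:

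- Make the primary estimate a standardised (g-computation) risk difference from a logistic model with treatment, centre, and baseline bilirubin and age as continuous terms. Add baseline albumin if it is recorded at randomization.
- Fix before unblinding the rule for pooling small centres, and state a simple rule for missing baseline values.
- Do not adjust for type of surgery, which is settled at exploration, or for tumour pathology known only after surgery.
- Compare the one-sided 95% upper limit of the risk difference with the 10-point margin, and report the relative risk from the same model.
- Keep the crude comparison as a sensitivity analysis.

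The cost is a short addition to the plan and slightly more analysis work, with no extra patients. The downside is a possible small loss of power if the covariates prove not to be prognostic.

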### Study design

The DROP-trial is a randomized multicenter trial with four academic and ten regional hospitals participating in the project. Patients with obstructive jaundice (bilirubin level 40–250 μmol/l) due to a pancreatic/periampullary tumor, who are candidate for exploration after staging with CT scan, and scheduled to undergo a "curative" resection, will be randomized to either "early surgical treatment" (within one week) or "preoperative biliary drainage" (for four weeks) and subsequent surgical treatment (standard treatment) (figure 1). Randomization is centralized in the Academic Medical Center, Amsterdam, by means of a computer generated allocation with stratification for center.

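### Success is a 10-percentage-point margin tested one-sided at 0.05, but the principal result is a relative risk with a 95% CI, which cannot show whether that margin was met

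*Protocol article*

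**What the plan says.** **Criterion.** Under *Sample size calculation*, and in the same sense in the abstract, equivalence is shown if "the percentage of severe complications with early surgical treatment is not more than 10% higher compared to standard treatment with PBD". Only the upper side is bounded, and the text does not say whether the 10% is absolute or relative.

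**Size.** "Accounting for a 10% dropout, 105 patients are needed in each arm", "resulting in a study population of 210 (alpha = 0.95, beta = 0.8"). The two labels can only be a confidence level of 0.95 and a power of 0.80.

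**Expected rates.** The abstract has "Based on a 40% complication rate for early surgical treatment and 48% for preoperative drainage". The sample size section has "Based on an expected 38% complication rate for early surgical treatment and 48% for preoperative drainage".

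**Analysis.** *Data analysis* says of the principal comparison: "The comparison will be expressed in terms of a relative risk and 95% confidence intervals". The next sentence evaluates the research hypothesis by a "two-group large-sample normal approximation test of proportions, with a one-sided 0.05 significance level". The article gives no limit for the relative risk, plans no interval for the risk difference, and does not state the null value of the test.

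**Randomisation.** Allocation is "by means of a computer generated allocation with stratification for center" (*Study design*). The stated test is a plain two-group comparison.

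**The concern.** In a trial judged against a margin, readers look at whether the confidence limit lies inside it. Here the margin is a difference in percentages and the planned interval is a ratio, so there is no line to read it against. Its confidence level is also stricter than that of the planned test. The result section could therefore report a passed test beside an interval that neither confirms nor contradicts it.

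The stakes are considerable. *Sample size calculation* lets the secondary outcomes choose the preferred strategy if equivalence is found, and *Economic evaluation* makes cost-minimisation depend on it. If the deciding scale and level are settled only after outcomes are known, that choice can change the primary conclusion.

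**Working it through.** **1. Reproduce the stated size.** Inputs: PBD 48%, early surgery 40% (abstract); margin 0.10; one-sided 0.05 (*Data analysis*); power 0.80; dropout 10%.

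- Formula: n = [p₁(1−p₁) + p₂(1−p₂)] × (z₁₋α + z₀.₈₀)² / (margin − expected difference)²
- Variance term: 0.48×0.52 + 0.40×0.60 = 0.4896
- Distance from the margin: 0.10 − (0.40 − 0.48) = 0.18
- n = 0.4896 × (1.645 + 0.842)² / 0.18² = 93.4, so 94 evaluable; 94/0.90 = 104.4, so **105 per arm, 210 in total**, an exact match.

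Alternative readings:

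| Reading | Evaluable per arm | Randomised per arm |
|---|---|---|
| Absolute 10 points, 48/40, one-sided 0.05 | 94 | **105** |
| Absolute 10 points, 48/38, one-sided 0.05 | 75 | 84 |
| Absolute 10 points, 48/40, one-sided 0.025 | 119 | 133 |
| Absolute 10 points, 48/38, one-sided 0.025 | 96 | 107 |
| Relative 10% (4.8 points), 48/40, one-sided 0.05 | 185 | 206 |
| Relative 10% (4.8 points), 48/38, one-sided 0.05 | 137 | 153 |

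Only the first gives 105. The fourth comes close, but not at the stated alpha. The margin is therefore absolute.

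**2. Scale.** Ten points as a relative risk is (PBD rate + 0.10) / PBD rate:

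- PBD 30%: 0.40/0.30 = 1.33
- PBD 48%: 0.58/0.48 = 1.21
- PBD 60%: 0.70/0.60 = 1.17

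The limit moves with a rate that is known only at the end. Fixing it at 1.208 would not rescue the ratio. By exact enumeration at 94 per arm and a true excess of 10 points, a 90% CI for the relative risk read against 1.208 would wrongly accept in 1.6% of trials at a PBD rate of 30% and in 9.8% at 60%. The risk-difference rule gives 4.9% at both. The 1.208 rule is hypothetical; the article does not contain it.

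**3. Level.** A two-sided 95% CI leaves 2.5% in each tail. The interval that corresponds to a one-sided 0.05 test is the two-sided 90% CI.

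**4. Power on the risk-difference scale, null at +10 points.** Power = Φ(distance/SE − z).

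- 48/40, 94 per arm: SE = √(0.4896/94) = 0.0722; 0.18/0.0722 = 2.494. One-sided 0.05: Φ(2.494 − 1.645) = 80.2%. One-sided 0.025: Φ(2.494 − 1.960) = 70.3%.
- 48/38, 94 per arm: variance term 0.2496 + 0.2356 = 0.4852; SE = 0.0718; 0.20/0.0718 = 2.784. One-sided 0.05: 87.3%. One-sided 0.025: 79.5%.
- If all 105 per arm are analysed, the one-sided 0.025 figures are 75.0% (48/40) and 83.7% (48/38).

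**5. One possible data set.** Early surgery 42/94 (44.7%), PBD 45/94 (47.9%). The difference is −3.2 points with SE 0.0727.

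- 90% upper limit: −0.0319 + 1.645×0.0727 = +8.8 points, inside the margin.
- 95% upper limit: −0.0319 + 1.960×0.0727 = +11.1 points, outside it.
- Planned report: relative risk 0.93, 95% CI 0.69 to 1.27. Nothing in that line shows that the criterion was met.

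**6. Centre.** The share of variance removed by stratifying is SD²/(0.44×0.56), where 0.44 is the mean of 40% and 48%. Assumed between-centre SDs of 10 and 15 points give 0.0100/0.2464 = 4% and 0.0225/0.2464 = 9%. At 94 per arm and 48/40, power would rise from 80% to about 82% and 83%. The documents do not give the spread.

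**The case against.** The strongest defence is that the article assigns the two roles itself. One sentence says how the comparison is expressed; the next says how the hypothesis is evaluated, by a one-sided 0.05 test. The interval describes and the test decides. *Data analysis* opens by calling the study an equivalence trial for the primary outcome, and equivalence is defined by the 10-point margin, so the natural null of the test is +10 points. The exact match of 105 supports this, and a condensed article need not spell out the null.

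Most of this stands. It rules out three stronger readings that a reader might infer:

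- *Reporting a relative risk costs power.* It does not. The stated test, with its null at +10 points, keeps about 80%. The lower figures apply only if a 95% interval is used to decide, which the article does not say.
- *The trial would be decided against a relative risk limit such as 1.21 or 1.10.* Neither appears in the article, and the sample size excludes the relative reading of the 10%.
- *The test is an ordinary test of equal proportions.* The wording leaves this open, but the design label and the sample size point the other way.

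The defence does not repair the mismatch. The effect measure and confidence level are stated choices, not details left to another document, and they do not fit the stated criterion. Leaving the null unstated matters more here because the reported interval cannot stand in for it.

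**Conclusion.** The point holds as a mismatch between criterion and reported result. Success is an absolute +10-point limit at one-sided 0.05; the planned summary is a relative risk with a 95% CI. It differs in scale and in level and has no stated limit, so it cannot show whether the margin was met.

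The effect on power is conditional. It is nil if the one-sided 0.05 test against +10 points decides. If a 95% CI on the risk difference decided, power at 94 evaluable per arm would be about 70% with the abstract's 40%, and 79.5%, practically the planned level, with the sample size section's 38%. These figures rest on the normal approximation with unpooled variance and a PBD rate of 48%. The conflict between 40% and 38% needs its own correction, since only 40% reproduces 105 at the stated alpha.

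Ignoring centre in the test is a minor matter. The gain from stratifying is small and its size rests on an assumed spread.

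**What to change.** In *Data analysis*, replace the sentence on the relative risk and the one on the test with text to this effect:

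> The primary estimate is the difference in the proportion with severe complications (early surgery minus PBD) with a two-sided 90% confidence interval. This corresponds to the one-sided 0.05 test of the null hypothesis that early surgery is at least 10 percentage points worse. The criterion is met if the upper limit lies below +10 percentage points. The relative risk with its 95% confidence interval is descriptive.

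Write percentage points instead of % for the margin in the abstract and in *Sample size calculation*. Compute the test and the interval with the same standard error so that they cannot disagree.

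As a secondary improvement, stratify the risk difference by centre (Mantel-Haenszel), as the randomisation already is. The method copes with many small strata.

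The cost is wording only: no further patients or data, and 105 per arm stands. The change should be made before outcomes by arm are seen. If the sponsor would rather let a 95% CI on the risk difference decide, 80% power needs 133 per arm (266 in total) at 48/40 or 107 per arm (214 in total) at 48/38.

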## Background

Patients with obstructive jaundice caused by a tumor in the pancreatic head area (pancreas, distal bile duct, papilla of Vater), without radiological evidence of irresectability, will undergo an exploration with the intention of resection of the tumor, being the only option for cure [1-4]. If a resection is not possible due to locoregional irresectability or distant metastases, a biliary and gastric bypass procedure is performed [5-8]. Surgery in jaundiced patients with a tumor in the pancreatic head area is associated with a higher risk of postoperative complications compared with surgery in non jaundiced patients [9-11]. These complications primarily consist of septic complications (cholangitis, abscesses, and leakage), haemorrhage, impaired wound healing and renal disorders. The increased risk of surgery in jaundiced patients was recognized already in 1935 by Allen O. Whipple, who proposed a two staged procedure for surgery in deeply jaundiced patients. The first stage consisted of a drainage procedure by a cholecystogastrostomy, to decompress the biliary tract in order to restore normal liver function, followed four weeks later by radical resection of the tumor [12]. Numerous experimental and clinical studies have been performed since, investigating the cause and directed at prevention of complications after surgery in patients with obstructive jaundice.

While the postoperative mortality rate after pancreatoduodenectomy has been reduced from around 20% to 1–5% in experienced centres, the morbidity rate has remained virtually unchanged, ranging from 40 to 60% [5,6,8,9]. Many different etiologic factors for development of complications have been characterized: presence of toxic substances as bilirubin and bile salts, impaired nutritional status, effects of endotoxins, bacterial translocation, modulation of the inflammatory cascade with cytokine release, reduction of cellular immunity and nutritional status [13-21]. For these etiologic factors different interventions have been undertaken in the past decades, attempting to lower the risk of complications. The current project addresses the issue of preoperative biliary drainage (PBD).

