### Study outline

Patients may be included if CT scan has demonstrated a lesion in the pancreatic head area without metastases and/or local tumor ingrowth. Local physicians/gastroenterologists can refer patients for the study by contacting the primary trial centre or one of the participating centres (see addendum 1). Written informed consent will be obtained at the outpatient department according to the Guidelines of Clinical Research in Humans, when the patient meets the in- and exclusion criteria. Randomization is performed instantly by the trial centre.

After randomization, patients will be scheduled, either for surgical treatment within one week, or PBD with subsequent surgical treatment after four weeks. PBD is preferably performed by local gastroenterologists or in the referral centre according to local policy. The participating centres accepted to arrange extra operating room capacity to guarantee early surgery to be carried out when indicated.

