#### ERCP + PBD

- ERCP with stent placement will be performed by an experienced endoscopist, by insertion of a single (plastic) stent

- If ERCP is not successful, the patient is to be referred to a tertiary centre for a second attempt for endoscopic drainage, or a percutaneous drainage will be performed, according to local preference and expertise.

- Biliary drainage is considered adequate if a decrease of > 50% of serum bilirubin level is found after two weeks of drainage; otherwise the stent should be changed.

- After four weeks of PBD, patients will undergo surgery. In case of complications indicating inadequate bile drainage and stent obstruction (cholangitis, stent occlusion) a stent exchange will be performed.

- Other complications, such as bleeding or severe pancreatitis, are treated according to the local generally accepted guidelines and could consequently lead to a delay of surgery [35,36].

- Preoperative nutritional support (e.g. consultation with a dietician) is recommended in patients with a weight loss of more than 15% during the last 3 months.

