#### Surgery

- Surgery is planned keeping in mind the maximum estimated bilirubin level (> 40 μmol/l and < 250 μmol/l at randomization) must not exceed 300 μmol/l, 24 hours before surgery (e.g. high bilirubin at randomization requires earlier surgery).

- Vitamin K (10 mg, oral, 1 day preoperatively) is given on indication, cefuroxim (1500 mg, intravenous single shot, 1/2 hour preoperatively) and octreotide or analogues (3 × 100 μg, subcutaneous, 12 hours before surgery and continued for seven days after surgery) as prophylaxis.

- During exploration the standard procedure will be the standard pylorus preserving pancreatoduodenectomy (PPPD), as previously described, with removal of lymph nodes at the right side of the portal vein [33]. If indicated (suspicious ingrowth proximal duodenum/pylorus) a Whipple procedure is to be performed. In case of limited vascular ingrowth, a (wedge) resection of the portal/mesenteric vein might be performed [33,41].

- Reconstruction is performed by pancreaticojejunostomy, a hepaticojejunostomy and gastrojejunostomy [33].

- One silicone drain is placed near the pancreaticojejunostomy and/or one near the hepaticojejunostomy; T-drains will not be used.

- A feeding jejunostomy is not to be used as standard treatment

- If resection is not performed due to metastases or local ingrowth, biopsies have to be taken for a histological diagnosis.

Palliative treatment consist of a hepaticojejunostomy with gastroenterostomy plus a celiac plexus blockade [7,33,42]. If a hepaticojejunostomy is not possible, a Wallstent is inserted postoperatively by means of ERCP.

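### Resection versus bypass, a preplanned subgroup, is settled after randomisation and can depend on the assigned strategy, so comparing the arms within it is open to bias

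*Protocol article*

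**What the plan says.** The Data analysis section of the protocol article lists its subgroups in one sentence: "Preplanned subgroup analyses include type of surgery (resection versus bypass), severity of jaundice and other risk factors for complications". The list continues with age, weight loss, albumin, renal function, haemoglobin and tumour pathology. Type of surgery comes first, with no note that it differs in kind from the others.

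Other sections show when that variable acquires a value:

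- Under Study design and Study population, patients enter after CT staging, as candidates for exploration with a curative resection planned. The CT may be at most 4 days old at randomisation.
- Study outline gives the schedule by arm: "patients will be scheduled, either for surgical treatment within one week, or PBD with subsequent surgical treatment after four weeks".
- The ERCP + PBD section says that other drainage complications, such as bleeding or severe pancreatitis, "are treated according to the local generally accepted guidelines and could consequently lead to a delay of surgery".
- Background states the alternative to resection: "If a resection is not possible due to locoregional irresectability or distant metastases, a biliary and gastric bypass procedure is performed". The Surgery section gives the same reasons: "If resection is not performed due to metastases or local ingrowth, biopsies have to be taken for a histological diagnosis".

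The main comparison is separate from all this: "The principal analysis consists of an intention-to-treat comparison of the severe complication rate in both treatment strategies".

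**The concern.** A subgroup comparison between arms keeps the protection of randomisation only if membership is fixed before assignment, or at least cannot be changed by it. Resection versus bypass is unknown for every patient at randomisation. It is then determined at different times in the two arms, after different preoperative courses. Those resected after early surgery need not be the same kind of patient as those resected after drainage and a wait of four weeks or more. Patients never operated on belong to neither subgroup.

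What is at stake is the reading of a secondary result. The Discussion puts the question in terms of drainage before a pancreatoduodenectomy, so a result in resected patients could be taken as the direct answer, and calling it preplanned would lend it weight. Such a comparison could show a difference between strategies where there is none, or hide one that exists.

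**Working it through.** **No plan figure to reproduce.** The article gives no resection rate, no expected complication rate by procedure and no size for this subgroup. The sample size of 105 per arm does not depend on it. The first two steps therefore rest on the text, and the third is an assumed illustration.

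**Step 1: is the variable known at randomisation?** No. All patients enter with resection planned. Metastases or local ingrowth that rule it out lead to bypass, and the Surgery section places that decision at exploration.

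**Step 2: can assignment change it?** Yes, in principle.

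- As scheduled, the operation comes within one week in one arm and after four weeks in the other. That is a gap of at least 4 - 1 = 3 weeks, longer if drainage complications delay surgery.
- The stated reasons for not resecting concern tumour extent, which can change over that interval.
- Under Primary outcome parameter and Table 1, severe complications include those of the drainage procedure. A primary-endpoint event in the drainage arm can therefore come before surgery, delay it, and so precede the subgroup classification.

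**Step 3: how large could the distortion be?** Divide patients into three kinds: resectable at either time, resectable early but not after the wait (share S of all patients, risk r), and never resectable.

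Inputs:

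- Risk of 48% in patients resectable at either time. The figure is the article's expected drainage-arm rate; applying it to this group is an assumption.
- 70% resectable if operated on early (assumed).
- S from 5% to 15% (assumed).
- r from 30% to 70% (assumed).
- Risk of 30% in the never resectable (assumed).
- Each patient's risk is the same under both strategies, so the true effect is zero. All patients are operated on.

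Formulas:

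- Resected, early: [(0.70 - S) × 0.48 + S × r] / 0.70. Resected, drainage: 0.48. Difference: S × (r - 0.48) / 0.70.
- Bypassed, early: 0.30. Bypassed, drainage: (S × r + 0.30 × 0.30) / (S + 0.30). Difference: -S × (r - 0.30) / (S + 0.30).
- All randomised, either arm: (0.70 - S) × 0.48 + S × r + 0.30 × 0.30. Difference: 0.

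Worked case, S = 0.15 and r = 0.70:

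- Resected: (0.264 + 0.105) / 0.70 = 52.7% v 48.0%, difference +4.7 points.
- Bypassed: 30.0% v (0.105 + 0.090) / 0.45 = 43.3%, difference -13.3 points.
- All randomised: 0.264 + 0.105 + 0.090 = 45.9% in both arms.

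Early-minus-drainage differences in percentage points:

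| S | r | Resected | Bypassed |
|---|---|---|---|
| 5% | 30% | -1.3 | 0.0 |
| 5% | 70% | +1.6 | -5.7 |
| 10% | 30% | -2.6 | 0.0 |
| 10% | 60% | +1.7 | -7.5 |
| 10% | 70% | +3.1 | -10.0 |
| 15% | 30% | -3.9 | 0.0 |
| 15% | 48% | 0.0 | -6.0 |
| 15% | 70% | +4.7 | -13.3 |

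At S = 0 both differences are zero.

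**The case against.** The strongest reply is that bias is possible but not shown. It requires the strategy to change who is resected, and the article gives no share of patients for whom that happens. If nobody switches, the mechanism in the illustration disappears. This stands, and it is why the point is worded as open to bias. A reader might also infer that the subgroup would be tilted against early surgery. The documents do not support that, because the sign in the resected group depends on whether switching patients carry a higher or lower risk than the others.

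A second reply is that type of surgery is listed beside risk factors for complications and that no between-arm test is specified, so a descriptive breakdown may be all that is meant. That reading is not excluded. However, nothing in the text limits the analysis to description, and the variable stands in the same list as baseline factors such as age.

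Third, it is one secondary analysis. This also stands. A reader might set the apparent differences against the 10-point margin and conclude that the equivalence finding is at risk. The margin belongs to the primary comparison, which is by intention to treat, and no margin or decision rule attaches to any subgroup.

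Finally, a reader might extend the charge to severity of jaundice, albumin, renal function and haemoglobin, since drainage is meant to alter the patient's condition and its adequacy is judged by a bilirubin fall of more than 50%. That would hold only if preoperative values were used. The article does not say so, and the bilirubin eligibility range is explicitly taken at randomisation. The measurement time may properly be left to the full protocol or analysis plan, so this is not part of the finding.

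**Conclusion.** The point holds in a limited form. The article preplans a subgroup whose membership is determined after randomisation, at different times in the two arms, and which the assigned strategy can influence. Arms compared within resected or within bypassed patients are therefore not randomised groups. This structural conclusion rests on the text alone, and no choice of test would cure it.

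The size cannot be derived from the documents. Under the stated assumptions, spurious differences of -3.9 to +4.7 points in the resected and 0 to -13.3 points in the bypassed arise with no true effect in any patient. These ranges show what the design permits and are not a forecast. The primary analysis and the sample size are unaffected. The correction is worth making because it is nearly free and prevents a misleading comparison.

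**What to change.** In the Data analysis section, remove type of surgery from the treatment-effect subgroups. In its place:

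- report the resection rate by arm, with all randomised patients in the denominator, so that those bypassed and those never operated on are counted;
- report severe complications by procedure descriptively, without between-arm tests, and state that the grouping arises after randomisation;
- state that treatment-effect subgroups use variables known at randomisation.

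The cost is a change of wording, with no effect on sample size or conduct. The downside is that there is no formal comparison of the strategies within resected patients, which some readers will want.
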